### Sample size

Sample size calculation was performed by using the stata software. For the subgroup of people with HbA1c ≥ 7%: assuming the difference of 0.4% between the control and intervention group (7.8% vs 7.4%) [4] and the standard deviation of 0.94% as observed within this subgroup at the baseline data analysis, we would need 232 people in both arms to achieve a power of 0.90 in this subgroup. 46% of the participants represent this group. This means that recruiting 555 people in total would be enough to power our hypothesis for the subgroup of people with HbA1c ≥ 7% at baseline if accounting for up to 10% drop-out.

For the total study population: based on the assumption that the mean difference in HbA1c between two groups will be of 0.3% (7.0% vs 6.7%) [2], and standard deviation of 1.05% - as analyzed at baseline – to achieve a power of 0.90 with alpha being 0.05, we would require 514 subjects to complete the study. Allowing for a dropout rate of up to 10%, the target recruitment number should be 566 patients totally, or 283 patients in each arm [27].

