### Statistical analysis

The two-tailed unpaired t-test will be used for continuous data and chi-square test for proportions. Where appropriate, regression analysis will be applied to account for baseline differences between the two study groups. The results will be expressed as mean (95% CI) for normal data and median (range) for skewed data. Sensitivity analysis will examine the effect of loss to follow-up on the intervention effect. The analysis will be conducted by intention to treat, which means, all patients will be followed for the full duration of the trial. Exploratory analyses will examine the effect of other factors, such as socio-demographic variables, on the outcome.

ICERs will be calculated for the mean and for the upper and lower confidence levels of marginal costs and utilities. One-way sensitivity analysis will be performed to test the relative contribution of different variables to the uncertainty around ICER and presented by means of a Tornado diagram. Probabilistic sensitivity analysis (Monte Carlo simulation) will be performed for all model inputs. The structural uncertainty will be tested through presenting different model scenarios. The results of this analysis will be presented on the cost-effectiveness plane. Probability of willingness to pay by the Belgian Health Care system will be forecasted and presented as a cost-effectiveness acceptability curve [30].

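### The 90% power for the HbA1c ≥ 7% subgroup rests on a baseline SD narrowed by selection; an unadjusted 6-month t-test has about 84–87% if the whole-group SD stays at 1.05%

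*Protocol article*

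**What the plan says.** The Sample size section of the protocol article makes two power statements.

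- **Subgroup with HbA1c ≥ 7%.** It plans "assuming the difference of 0.4% between the control and intervention group (7.8% vs 7.4"%), takes "the standard deviation of 0.94% as observed within this subgroup at the baseline data analysis", and concludes "we would need 232 people in both arms to achieve a power of 0.90 in this subgroup".
- **Total population.** It plans a difference of 0.3% with a "standard deviation of 1.05% - as analyzed at baseline", "to achieve a power of 0.90 with alpha being 0.05".

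The Study design section sets the primary outcome as HbA1c at 6 months after randomization, with 1:1 allocation. The recruitment and randomization section shows that the 7% cut is applied to baseline HbA1c and is also the randomization stratum.

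The Statistical analysis section says "The two-tailed unpaired t-test will be used for continuous data and chi-square test for proportions". The next sentence adds "Where appropriate, regression analysis will be applied to account for baseline differences between the two study groups".

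**The concern.** The subgroup is formed by cutting the baseline HbA1c distribution at 7%. Its baseline SD therefore comes from a truncated distribution and is smaller (0.94%) than the SD of everyone (1.05%). At 6 months nobody is selected again: some patients who entered above 7% will be below it, and the spread tends to move back toward that of the unselected group. The power calculation carries the truncated SD over to the 6-month values.

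The two paragraphs of the Sample size section also fit together poorly. One plans the 6-month outcome in the whole group with 1.05%; the other plans the same outcome in the selected subgroup with 0.94%. Under a linear relation with constant variance, both can be true only if baseline and 6-month HbA1c correlate perfectly. The planned control mean of 7.8% points the same way, because it equals the usual-care subgroup's baseline mean in Table 2. The selected baseline distribution is in effect being used as the follow-up distribution.

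The stake is interpretation. The subgroup has its own hypothesis and power statement, so a null result there would be read as coming from a test with 90% power.

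**Working it through.** **Inputs from the protocol article.** Difference 0.4; subgroup baseline SD 0.94; whole-group baseline SD 1.05; 232 completers, so 116 per arm at 1:1; two-sided unpaired t-test. Alpha of 0.05 is stated for the total population and is taken to apply to the subgroup too.

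**Assumptions not in the documents.** The correlation r between baseline and 6-month HbA1c; the whole-group 6-month SD, S; a linear relation with constant residual variance.

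**Step 1: reproduce the stated figure.** n per arm = 2 × [0.94 × (1.960 + 1.282) / 0.4]² = 116.05, or 232 in total when rounded to the nearest whole number. With 116 per arm, power is 0.900 by the normal approximation and 0.897 by the noncentral t. The protocol's arithmetic is correct for its inputs, and it matches an unadjusted comparison.

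**Step 2: 6-month SD in the selected subgroup.** Selection shrinks the baseline variance by the factor (0.94/1.05)² = 0.801. Only the part of the 6-month variance explained by baseline shrinks with it:

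SD_sub = S × √[1 − r² × (1 − 0.801)]

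With S = 1.05 this equals √[r² × 0.94² + (1 − r²) × 1.05²].

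**Step 3: power of the unadjusted t-test** (S = 1.05, 116 per arm, noncentral t):

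| r | SD_sub | Power |
|---|---|---|
| 0 | 1.05 | 82.4% |
| 0.5 | 1.02 | 84.2% |
| 0.6 | 1.01 | 85.0% |
| 0.7 | 1.00 | 86.0% |
| 0.8 | 0.98 | 87.1% |
| 1 | 0.94 | 89.7% |

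By the normal approximation, 90% power would need 276 completers at r = 0.5 and 254 at r = 0.8, against 232 planned.

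**Step 4: vary the assumed 6-month SD** (r from 0.5 to 0.8):

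| S | Power, unadjusted t-test |
|---|---|
| 0.95 | 90.6% to 92.8% |
| 1.05 | 84.2% to 87.1% |
| 1.10 | 80.8% to 83.9% |

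Setting SD_sub back to 0.94 and solving for S gives 0.94 / √[1 − r² × 0.199], which is 0.96 at r = 0.5 and 1.01 at r = 0.8. A whole-group SD that fell from 1.05 to that level would make the protocol's figure right.

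The constant-variance assumption matters as well. In a right-skewed simulation with a baseline subgroup SD of about 0.90 and correlations of about 0.5 to 0.9, power was about 76–87%, so 84–87% is not a bound.

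**Step 5: adjust for baseline HbA1c.** The residual SD is S × √(1 − r²), which selection on baseline does not change. With S = 1.05:

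| r | Residual SD | Power |
|---|---|---|
| 0.5 | 0.91 | about 92% |
| 0.6 | 0.84 | about 95% |
| 0.7 | 0.75 | about 98% |
| 0.8 | 0.63 | over 99% |

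At S = 1.10 and r = 0.5 the residual SD is 0.95 and power is about 89%. The 6-month SD therefore needs stating for the adjusted analysis too.

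**Step 6: patients available.** Table 2 implies (287 − 155) + (287 − 159) = 132 + 128 = 260 patients in the subgroup. After 10% dropout, 260 × 0.9 = 234 remain, so the planned 232 is met but with almost no margin.

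**The case against.** A reader might infer that the true power is 84–87%, or that it must fall short of 90% whatever the correlation. The documents support neither. They give no 6-month SD and no correlation, and the direction holds only while the whole-group 6-month SD stays near 1.05%. A drop of 4–8% in that SD would restore 90%. Such a drop is not far-fetched: coaching works toward targets, and laboratory results go to all patients and their GPs. This part of the objection stands, so the figures must be given as conditional. Against it, 1.05% is the value the protocol itself uses to plan the same outcome, and the protocol assumes no narrowing.

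The 0.94% is also only an estimate. With about 260 patients, an approximate normal-theory 95% interval is 0.87–1.03%, which covers the alternative SDs of 0.98–1.02%. Planning from an observed baseline SD is common, and the article labels it openly. That is fair, but sampling error runs both ways, whereas truncation narrows the baseline spread.

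It would also be wrong to say that the plan offers only an unadjusted test. Regression is foreseen, and its details may properly sit in an analysis plan that is not shown. But the stated trigger is baseline differences between groups, and randomization stratified on HbA1c makes a difference on that variable less likely. The subgroup power figure names no covariate or correlation.

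Finally, the consequence is small. The total-population target (566) exceeds the subgroup's (555), and 574 patients were assessed at baseline. If all 260 subgroup patients were analysed, the SDs in Step 3 for r = 0.5 to 0.8 would give 88–91%. That stands, and it is why this is a minor point.

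**Conclusion.** The point holds in conditional form. The 0.90 is correct arithmetic on an SD that belongs to a truncated baseline distribution rather than to the 6-month outcome. The loss for an unadjusted t-test is about 3 to 6 percentage points if the whole-group 6-month SD is 1.05%, the correlation is 0.5 to 0.8, and the relation is linear with constant variance. Under that model power stays above 80% at any correlation and reaches the stated figure only at a correlation of 1. A smaller 6-month SD would remove the shortfall; a larger SD or marked skewness would deepen it.

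It should not be read as showing that the trial is underpowered. It concerns one subgroup and does not touch the total-population calculation.

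**What to change.** Make the 6-month HbA1c comparison in this subgroup baseline-adjusted as the planned analysis: ANCOVA with baseline HbA1c as covariate, not regression at discretion. Attach the 90% power statement to that analysis, and state the assumed correlation and 6-month SD beside it.

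If the unadjusted t-test is kept as the planned analysis, replace the single figure with a conditional range: about 84–87% for correlations of 0.5 to 0.8 at a whole-group 6-month SD of 1.05%, with the sensitivity to that SD shown.

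The cost is a reworded power statement and one covariate that is already collected at baseline.

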## Methods/Design

### Study design

The study is a parallel-group RCT, in which patients with type 2 diabetes, affiliated to the Belgian sickness fund Partena, were selected based on their medication consumption data, recruited by their sickness fund, and randomized to receive usual care plus The COACH Program or the usual care alone. The study will assess the difference in outcomes between the two groups. The primary outcome measure is the level of glycohemoglobin HbA1c at 6 months after randomization. The secondary outcomes are: total cholesterol (TC), low-density lipoprotein (LDL), high-density lipoprotein (HDL), triglycerides (TG), blood pressure (BP), Body Mass Index (BMI), smoking status; proportion of people at target for HbA1c, LDL-Cholesterol and Blood Pressure; self-perceived health status, diabetes-specific emotional distress, and satisfaction with diabetes care. The follow-up period is 18 months. All outcome measurements will be collected 3 times: before randomization, upon the graduation from the program (6 months after the program start); and at the end of the follow-up period (18 months after randomization). The allocation ratio is 1:1. Within-trial and modeled cost-utility analyses, - to project effects over a longer time horizon beyond the trial duration, - will be undertaken from the perspective of the health care system if the intervention is effective.

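### Two HbA1c hypotheses are powered without saying which is confirmatory; if either could carry the main claim, the familywise error would be up to about 8.7%

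*Protocol article*

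**What the plan says.** All references are to the protocol article.

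- **Study design** names one primary outcome: "The primary outcome measure is the level of glycohemoglobin HbA1c at 6 months after randomization". It describes a comparison of the two randomised groups and mentions no subgroup.
- **Sample size** opens with the subgroup at baseline HbA1c of 7% or more. It assumes a difference of 0.4 points and "the standard deviation of 0.94% as observed within this subgroup at the baseline data analysis", and concludes that "we would need 232 people in both arms to achieve a power of 0.90 in this subgroup". With the subgroup at 46% of participants and up to 10% drop-out, it says 555 recruits "would be enough to power our hypothesis for the subgroup of people with HbA1c ≥ 7% at baseline".
- The same section then treats the total population, with a difference of 0.3 and a standard deviation of 1.05: "to achieve a power of 0.90 with alpha being 0.05, we would require 514 subjects to complete the study". The recruitment target of 566, or 283 per arm, comes from this second calculation.
- **Patient recruitment and randomization** stratifies on the same cut, HbA1c below 7% against 7% or above. Blocking is not described.
- **Statistical analysis** states "The two-tailed unpaired t-test will be used for continuous data", with regression for baseline differences where appropriate. It names no subgroup test and gives no order or split of alpha.
- **Cost-utility analysis** is carried out only if the trial shows a favourable clinical difference between the groups. The population in which that is judged is not stated.

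**The concern.** The subgroup is not presented as an exploratory look. It is called a hypothesis, comes first in its section, has its own effect size, power and recruitment total, and is the randomisation stratum. Yet the aims, the primary outcome and the analysis section do not mention it. The text therefore powers a hypothesis to which it gives no status.

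The two tests may disagree. With a null overall result and a positive subgroup, or the reverse, the article does not say which one governs. Either could be put forward as the powered result, and either might be read as opening the way to the cost-utility analysis, which is meant to inform reimbursement. If that choice were made after seeing the data, the 5% error rate would no longer apply.

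**Working it through.** **1. Reproducing the sample sizes.** Normal approximation, two-sided 0.05, power 0.90, 1:1 allocation; per arm n = 2(1.960 + 1.282)² × SD² / difference², with (1.960 + 1.282)² = 10.507.

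- Subgroup: 2 × 10.507 × 0.94² / 0.4² = 116.05 per arm. The stated total is 232 = 2 × 116.
- All patients: 2 × 10.507 × 1.05² / 0.3² = 257.4 per arm. The stated total is 514 = 2 × 257.

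Rounding up per arm gives 234 and 516, so both stated figures reproduce. Alpha is written only for the total population. One-sided 0.05 would need about 190 in the subgroup, so 232 implies a full, unsplit two-sided 0.05 there too.

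**2. Familywise error if either test could carry the claim.** The subgroup is part of the total, so the two statistics are correlated. Ignoring stratification, correlation = √(subgroup share) × SD(subgroup) / SD(all), with a share of 0.46:

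- equal SDs: √0.46 = 0.678
- the article's SDs: 0.678 × 0.94 / 1.05 = 0.607

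Error = 1 − P(|Z₁| < 1.96 and |Z₂| < 1.96) from a bivariate normal:

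| Correlation | Familywise error |
|---|---|
| 0.678 | 8.4% |
| 0.607 | 8.7% |
| 0 (limit) | 9.75% |

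**3. Allowing for the HbA1c stratum.** Assume balance within strata (blocking is not stated) and a standard deviation s in the below-7% stratum, which the article does not give. With stratum adjustment, correlation = √0.46 × 0.94 / √(0.46 × 0.94² + 0.54 × s²).

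| Assumed s | Correlation | Error, both tests at 0.05 |
|---|---|---|
| 0.30 | 0.945 | 6.5% |
| 0.45 | 0.888 | 7.2% |
| 0.60 | 0.822 | 7.7% |

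Under the same balance, an unadjusted t-test in all patients that uses the total SD of 1.05 is conservative. The either-test error is then about 5.0–5.2%.

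**4. Effect of a rule.** A fixed order, with all patients first, gives 5% with no change in size. Splitting alpha at 0.025 each gives 4.3% (correlation 0.678), but power at 232 and 514 completers falls to about 84% for each test.

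**5. Recruitment totals.**

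| | Subgroup | All patients |
|---|---|---|
| As stated (× 1.1) | 232 / 0.46 × 1.1 = 554.8, so 555 | 514 × 1.1 = 565.4, so 566 |
| Completers at 10% loss | 555 × 0.9 × 0.46 = 230 | 566 × 0.9 = 509 |
| Power at those completers | 89.7% | 89.7% |
| Correct (÷ 0.9) | 232 / 0.46 / 0.9 = 560.4, so 561 | 514 / 0.9 = 571.1, so 572 (286 per arm) |

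Table 2 shows 574 patients. Of these, 574 − 155 − 159 = 260 (45.3%) are at 7% or above. At 10% loss, 574 × 0.9 = 517 and 260 × 0.9 = 234, which meet 514 and 232.

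**The case against.** The strongest reply is that the article already has one primary comparison. Study design names a single outcome and compares the groups as randomised, the recruitment target comes from the all-patient calculation, and the analysis section names no subgroup test. Powering a subgroup does not make it a second route to the main claim. This stands. A reader might infer that the main claim carries a false-positive risk of 8.5–9%. The documents do not support that, because no either-test rule is stated and 9% is not reached on the article's own inputs.

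The size of the error is also open to challenge. Randomisation is stratified on this same cut, and Table 2 is close to balanced (132 against 128 at 7% or above). This also stands: depending on the analysis, the either-test figure could be 6.5–7.7%, or close to 5% with an unadjusted overall t-test. Because blocking is not stated and the lower-stratum SD is assumed, those lower figures are conditional too.

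A testing order may also sit in an analysis plan that is not shown, and its absence from an article is not in itself an error. What remains is internal to the visible text: it powers a hypothesis in the subgroup and gives that hypothesis no status.

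On recruitment, the shortfall is small and has no practical consequence. That is correct, and the point is kept only as a correction of figures.

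**Conclusion.** The point holds in conditional form. Two HbA1c hypotheses are powered at 90%, both at a full two-sided 0.05 (written for all patients, inferred from 232 for the subgroup), and the article does not say which is confirmatory.

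- If either could carry the main claim, the familywise error would be up to about 8.7%, assuming normal statistics, a 46% share and the stated SDs.
- With adjustment for the HbA1c stratum it would be about 6.5–7.7%, assuming balance within strata and lower-stratum SDs of 0.3–0.6.
- If the all-patient test alone is primary, it stays at 5%.

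The defect is therefore an ambiguity that leaves room for inflation, not a demonstrated inflation. It should be settled before analysis.

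The drop-out arithmetic is wrong whichever reading is taken, but it costs only about 0.3 points of power and the actual enrolment covers it.

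**What to change.** In Sample size and Statistical analysis, state that the comparison of HbA1c at 6 months in all randomised patients is the primary test at two-sided 0.05. Then choose one status for the subgroup at 7% or above: test it at 0.05 only if the primary test succeeds, or label it secondary and report it with the arm-by-stratum interaction. Either choice keeps the error of the main claim at 5% and leaves the sample size unchanged. The cost is a sentence or two, and no confirmatory subgroup claim if the overall test misses.

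Restate the recruitment totals as 561 in place of 555, and 572 (286 per arm) in place of 566. Only the printed figures change; no further recruitment is needed.

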### Patient recruitment and baseline data

Between April 2012 and June 2013, 3115 affiliates of the sickness fund Partena were identified based on the reimbursement data and invited into the study. 685 (22%) agreed to participate. 574 were eligible and took part in the baseline assessment. Figure 1 shows the RCT flowchart including the numbers of enrolled and randomized patients. Table 2 summarizes the baseline characteristics of people allocated to the intervention and control groups.

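### Both recruitment targets add 10% to the required number instead of dividing by 0.90, so at the stated 10% drop-out each falls slightly short of the plan's own requirement

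*Protocol article*

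**What the plan says.** The Sample size section of the protocol article makes two calculations.

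- **Total population.** With a difference of 0.3% HbA1c and a standard deviation of 1.05%, the text says: "to achieve a power of 0.90 with alpha being 0.05, we would require 514 subjects to complete the study". The drop-out step follows: "Allowing for a dropout rate of up to 10%, the target recruitment number should be 566 patients totally, or 283 patients in each arm".
- **Subgroup with HbA1c of 7% or more.** With a difference of 0.4% and a standard deviation of 0.94%, 232 people in the two arms together are needed for power of 0.90. The subgroup is taken as 46% of participants. The text concludes that "recruiting 555 people in total would be enough to power our hypothesis for the subgroup of people with HbA1c ≥ 7% at baseline", again with an allowance of up to 10% drop-out.

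The section on patient recruitment and baseline data reports the result of recruitment: "574 were eligible and took part in the baseline assessment". Table 2 shows 287 in each arm.

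**The concern.** The figure of 514 is explicitly a number of completers, and the drop-out rate is a fraction of those recruited. A target that allows for 10% loss must therefore still leave 514 after a tenth of the recruits have gone. Neither 566 nor 555 passes that test against its own requirement. All inputs and both results are printed in the same section, so the mismatch is in the article itself and does not depend on a fuller document.

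What is at stake is whether the printed allowance can be relied on. Follow-up runs to 18 months, and the Statistical analysis section plans a sensitivity analysis for loss to follow-up. Readers will compare actual attrition with the 10% that the plan says it can absorb.

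**Working it through.** **Inputs.** From Sample size: power 0.90 (both calculations); alpha 0.05 (stated for the total population, assumed the same for the subgroup); differences 0.3% and 0.4%; standard deviations 1.05% and 0.94%; 514 and 232 required; subgroup share 46%; drop-out up to 10%. From Statistical analysis: "The two-tailed unpaired t-test will be used for continuous data", so the test is two-sided. From Study design: "The allocation ratio is 1:1". From Table 2: 287 per arm, with 155 and 159 patients below 7% HbA1c.

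**Step 1: the base sizes reproduce.** The number per arm is 2 × (1.96 + 1.2816)² × SD² / d².

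- Total population: d = 0.3, SD = 1.05 gives 257.43 per arm, or about 515 in total (stated 514).
- Subgroup: d = 0.4, SD = 0.94 gives 116.05 per arm, or about 232 in total (stated 232).

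**Step 2: how the stated targets arise.**

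- 514 × 1.10 = 565.4, rounded up to 566. Per arm, 257 × 1.10 = 282.7, rounded up to 283.
- 232 / 0.46 = 504.3, and 504.3 × 1.10 = 554.8, rounded up to 555.

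Multiplication by 1.10 gives both stated integers exactly. Division by 0.90 gives neither.

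**Step 3: what the stated targets leave at 10% loss.**

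- 566 × 0.90 = 509.4, against 514 required.
- 555 × 0.46 × 0.90 = 229.8, against 232 required.
- Largest loss that each target absorbs: 1 − 514/566 = 9.2%, and 1 − 232/(555 × 0.46) = 9.1%.

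**Step 4: the effect on power.** With N completers in total, power is Φ[(d/SD) × √(N/4) − 1.96].

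- N = 509.4, d = 0.3, SD = 1.05: 0.897 (0.896 by the t-test).
- N = 229.8, d = 0.4, SD = 0.94: 0.897 (0.895 by the t-test).
- For comparison, the plan's own 514 and 232 each give just under 0.900 by the same formula.

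**Step 5: corrected targets.**

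- 514 / 0.90 = 571.1, rounded up to 572 (286 per arm). Check: 572 × 0.90 = 514.8.
- 232 / 0.46 / 0.90 = 560.4, rounded up to 561. Check: 561 × 0.46 × 0.90 = 232.3.

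Each stated target is 6 patients too low (572 − 566 and 561 − 555).

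**Step 6: the patients actually enrolled.**

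- Total population: 574 × 0.90 = 516.6, at least 514; power 0.901. The 514 are kept up to a loss of 1 − 514/574 = 10.5%.
- Subgroup by Table 2: (287 − 155) + (287 − 159) = 132 + 128 = 260. Then 260 × 0.90 = 234, at least 232; power 0.902. The 232 are kept up to a loss of 1 − 232/260 = 10.8%.

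**The case against.** The strongest reply is that nothing follows for the trial. The plan states power to two decimals, and 0.897 rounds to 0.90. The larger target governs recruitment, and 566 would still have left 566 × 0.46 × 0.90 = 234.3 in the subgroup, above 232. The 574 enrolled exceed both corrected targets. All of this stands, and it sets the size of the point. It does not make the printed figures right, because 566 is offered as the number that leaves 514 after 10% loss, and it leaves 509.

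One rescue is possible for 555 alone. If the unrounded share were close to 46.5%, then 232 / 0.90 / 0.465 = 554.4 would also round up to 555. The stated share is 46%, Table 2 gives 260/574 = 45.3%, and no such reading is open for 566. The common multiplier of 1.10 is the better explanation.

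A reader might also infer more than the document supports:

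- **That the trial is underpowered.** It is not on these inputs: 574 meets both requirements at 10% loss.
- **That the article claims a comfortable surplus over target.** It only reports that 574 took part. Subtracting 566 or 555 from 574 is the reader's own step.
- **That 90% power is lost as soon as loss passes 10%.** The 574 enrolled still leave 514 completers up to about 10.5% loss, and the change beyond that is gradual.
- **That the base sizes are wrong because they were rounded down.** Using 257 for 257.43 and 116 for 116.05 per arm costs 0.0005 of power or less.
- **That the 46% share is part of the same error.** The 0.7-point difference from Table 2 is a separate and minor matter of a planning figure against the final count.

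**Conclusion.** The point holds as an arithmetic slip in the drop-out step. Both targets were inflated by 1.10 where division by 0.90 was needed, and at the stated 10% drop-out neither leaves the number that the plan requires. The size is small: 6 patients per target and about 0.3 points of power. The completed recruitment is not affected, although the margin is thin.

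This rests on the plan's own differences and standard deviations, a two-sided alpha of 0.05 for both calculations, equal arms, and a loss in the subgroup equal to the overall loss.

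**What to change.** In Sample size, restate the overall target as 572 (286 per arm) and the subgroup target as 561 at the stated 46% share. Add one sentence: the 574 enrolled, of whom 260 are in the subgroup by Table 2, meet both completer requirements at 10% loss, with little margin (up to about 10.5% loss overall). The cost is two figures and one sentence. No patients, visits or analyses change.
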